## Abstract

**Introduction:**

Uganda’s community health worker (CHW), or village health team (VHT), program faces significant challenges with poor retention and insufficient financial and program investment. Adequate compensation comprising financial and non-financial components is critical to retaining any workforce, including CHWs. This study evaluates the impact of a recognition-based non-financial incentives package on the motivation, performance, and retention of VHTs, as well as on the utilization of health services by the community. The incentive package and intervention were developed in collaboration with the district-level leadership and award VHTs who have met predetermined performance thresholds with a certificate and a government-branded jacket in a public ceremony.

**Methods:**

A two-armed cluster randomized controlled trial (RCT), conducted at the parish level in Uganda’s Masindi District, will evaluate the effects of the 12-month intervention. The cluster-RCT will use a mixed-methods approach, which includes a baseline/endline VHT survey to assess the impact of the intervention on key outcomes, with an expected sample of 240 VHTs per study arm; our primary outcome is the total number of household visits per VHT and our multiple secondary outcomes include other performance indicators, motivation, and retention; VHT performance and retention data will be validated using monthly phone surveys tracking key performance indicators and through abstraction of VHT-submitted health facility reports; and focus group discussions will be conducted with VHTs and community members to understand how the intervention was received. Data collection activities will be administered in local languages. To assess the impact of the intervention, the study will conduct a regression analysis using Generalized Estimating Equations adjusting for cluster effect. Further, a difference-in-differences analysis will be conducted.

**Discussion:**

This study utilized a cluster-RCT design to assess the impact of a recognition-based incentives intervention on the motivation, performance, and retention of VHTs in Uganda’s Masindi District. Utilizing a mixed-methods approach, the study will provide insights on the effectiveness and limitations of the intervention, VHT perspectives on perceived value, and critical insights on how non-financial incentives might support the strengthening of the community health workforce.

**Trial registration:**

ClinicalTrials.gov NCT05176106. Retrospectively registered on 4 January 2022.

**Supplementary Information:**

The online version contains supplementary material available at 10.1186/s13063-023-07426-6.

## Background

Community health workers (CHWs) play a critical role in strengthening primary healthcare (PHC) globally—especially in rural areas, where there is often a shortage of skilled healthcare workers (i.e., physicians, nurses, and midwives, etc.). In Uganda, approximately 75% of the population is rural, while the majority of healthcare workers are concentrated in urban areas [1]. Uganda’s CHW program was launched in 2001 and has been scaled nationally—operating in all of Uganda’s 135 districts [2, 3]. Their CHW program comprises village health workers (VHWs) who work in teams of 5–6 people, which are known as “village health teams” (VHT) [2]. VHTs are a voluntary cadre, elected by the community members of their resident communities which they serve [2]. VHTs provide maternal, newborn, child health, and sanitation-related services. Since 2001, the VHT program has demonstrated positive impacts on health outcomes, particularly for communities that would otherwise lack access to health services [4–7]. Between 2001 and 2015, over 179,000 individual VHTs have been trained [3]. Like several CHW programs globally, the VHT program has faced many challenges due to high levels of attrition [8]. Lack of adequate compensation for their work and ongoing training, supervision, logistical, and financial support, as well as threats to personal health (e.g., COVID-19 pandemic, Ebola), are some of the core reasons why this cadre of health workers, which is so critical to the health of rural populations, experiences high rates of attrition [3].

The lack of remuneration for CHWs has been a longstanding debate within the field, with a growing push to compensate them fairly [9]. The 2018 *WHO Guideline on health policy and system support to optimize community health workers program* recommended remunerating CHWs with a “financial package commensurate with the job demands, complexity, number of hours, training, and roles that they undertake” [10]. In addition to financial remuneration, the WHO guideline recommends the provision of non-monetary incentives to further support and motivate CHWs [10]. In Uganda, the 2014 National VHT Assessment, which assessed the status and functionality of the VHT program, reported on the importance of providing VHTs with a “standardized and harmonized regular and equitable financial form of motivation” as well as the “equitable distribution of non-monetary incentives” [11]. Despite these recommendations, much progress is still to be made regarding the appropriate and equitable compensation (financial and non-financial) for VHTs.

A number of studies have assessed the effectiveness of a variety of non-financial and financial incentives on the performance and impact of CHW programs across settings with mixed results [10]. A cluster randomized controlled trial (RCT) which evaluated a non-monetary incentives intervention in India found that the provision of public recognition (through a ceremony and certificate) resulted in greater CHW motivation than the other non-monetary incentives provided [12]. In Uganda, one study found that the provision of non-financial incentives to CHWs—t-shirts, umbrellas, gumboots, and certificates, which were provided to all CHWs—resulted in improved CHW performance and motivation [13]. A 2021 systematic review on performance-based incentives reported that the provision of public recognition for CHW efforts resulted in increased and improved service delivery [14]. In Guinea-Bissau, CHWs received a certificate for good performance at a public ceremony; results from this study found increased satisfaction with CHWs by the community as well as increased community knowledge around health practices [15]. In contrast to these results, a 2021 study in Uganda that evaluated the effects of a competitive social reward (referring to a type of reward that provides public recognition) provided to the best-performing CHWs found a negative association between CHW performance and the provision of the social reward. The study provided a reward to 3% of the 4050 CHWs over the 3-year period [16]. The authors hypothesized that the negative results might be a consequence of the design of the award mechanism which has subjective eligibility criteria leading to perceptions of favoritism, infrequent award provision, and inadequate transparency regarding the selection process [16]. Despite this, the authors affirm that the provision of a recognition-based performance award can be effective towards improving CHW performance, with an emphasis placed on a transparent and fair award provision process [16]. None of these studies evaluated the effects of their intervention on CHW retention and attrition. Our current study builds on this evidence to assess the effectiveness of a package of non-financial recognition-based incentives on the performance, motivation, and retention of VHTs in Uganda. This study also builds on prior studies conducted in collaboration with the Johns Hopkins Bloomberg School of Public Health, Population Council and Pathfinder International, Uganda using a discrete choice experiment (DCE) study to understand incentive preferences of VHTs in Uganda [17]. The DCE study identified a variety of incentives desired by VHTs. In this study, in collaboration with district-level partners, we further define these incentives and prioritize those that are not only valued by VHTs but are also pragmatic and sustainable for government uptake. This protocol was developed in adherence to the SPIRIT checklist for reporting on protocols in clinical trials (see Additional file 1) [18].

The objectives of the present study are to better understand (1) the effectiveness of recognition-based non-financial incentives, to support VHT motivation, performance, and retention; (2) the behavioral mechanism through which new incentives may succeed or fail; and (3) the impact of improved VHT performance on the utilization of maternal and child health services, hygiene practices, and perceptions regarding the quality of health services at the community level.

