## Methods/design

We will conduct a two-armed cluster randomized, controlled superiority trial to evaluate the effects of the intervention on the motivation, performance, and retention of VHTs in Uganda’s Masindi District. The intervention comprises a recognition-based non-financial incentives package, designed in August 2021 in collaboration with local leadership from Masindi District; this process is described in further detail below.

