**Fig. 2 Fig2:**
[figure not shown]
The recognition-based incentives provided during the public ceremony to VHTs

All VHTs who have submitted their quarterly reporting forms (see Additional file 2) to the health facility will be considered for recognition. VHTs will be provided with regular reminders to submit quarterly reports to health facilities during VHT engagement activities (e.g., monthly VHT phone survey, health facility data abstraction). VHTs will be assigned to different strata based on the size of the rural/urban parishes (i.e., urban small, rural small, rural large) given the differences in the number of households and proximity of households. Finally, the top 10% of performers within each stratum will be publicly recognized. Performance of the VHTs will be assessed based on the following three indicators: the proportion of children under 5 years of age with up-to-date immunization, the proportion of sick children under 5 years of age the VHT has attended to, and the proportion of women who attended at least four antenatal care visits. These indicators were chosen as they are what VHTs record in and report from their registers and are likely to be achieved by VHTs. The denominators for each variable will be abstracted at the village level from the official population projection statistics provided by the Masindi District government, District Planner’s Office.

The public recognition ceremony will be convened on a quarterly basis, as the VHTs provide their activity reports on a quarterly basis. Representatives from the district will convene and lead the ceremony and all VHTs from the intervention parishes will be invited. For the comparison parishes, it will be standard practice, where VHTs continue to provide services as usual; there will be no public recognition ceremony for VHTs who are from the comparison parishes. Any changes to the intervention, if needed, will be made based on the input from the District; changes will be made at the intervention (status of randomization) level, and not at the VHT level, and will be documented for better contextual understanding. Intervention adherence will be facilitated by regular reminders to VHTs to submit quarterly reports to health facilities during VHT engagement activities (e.g., monthly VHT phone survey, health facility data abstraction).

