### Primary and secondary study outcomes

This study utilizes a mixed-methods approach to understand the impact of the intervention on the primary and secondary outcomes. The primary outcome of this study is changes in VHT performance (defined as the total number of home visits in the past three months). VHT performance is challenging to assess accurately as often VHTs may not have the tools to record their visits (e.g., registers), may not have received training to correctly record the information, and may not maintain records to accurately recall their activities. Therefore, VHT performance data will be collected in three specific ways: (1) through VHT surveys conducted at baseline and endline; (2) through the abstraction of quarterly reported data submitted to health facilities as VHTs are expected to report quarterly; and (3) through monthly phone surveys. Secondary outcomes for this study include the following: (i) VHT motivation (assessed using the validated Close-to-Close (CTC) Provider Motivational Indicator Scale [23]); (ii) VHT retention (measured through monthly self-reports); (iii) the other VHT performance measured by trends in service delivery; and (iv) trends in adoption of sanitary practices in each village. See Table 1 for the list of primary and secondary outcomes and the related data collection activities to measure them.

**Table 1 Tab1:** Primary and secondary outcomes and related data collection activities

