**Secondary outcomes**	
** 2. VHT motivation** *Measured through the CTC Provider Motivational Scale. This scale has four sub-modules on work satisfaction, organizational commitment, community commitment, and work conscientiousness*	VHT survey
** 3. VHT retention** *Assessed through the proportion of leaving VHTs*	VHT phone survey
** 4. Other VHT performance (trends in service delivery)** *No. of visits for antenatal care* *No. of visits for postnatal care* *No. of visits to support immunization of children* *No. of referrals made to health facility* *No. of sick under-5 children attended by a VHT* *No. of people provided with HIV counseling* *No. of people provided with TB counseling* *No. of people provided with general counseling*	VHT survey VHT phone survey Abstraction from health facility report
** 5. Trends in adoption of sanitary practices per village** *No. of households with latrines* *No. of households with improved latrines* *No. of households with handwashing facilities* *No. of households with safe drinking water* *No. of households that are open defecation free*	VHT survey Abstraction from health facility report

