#### Focus group discussions (FGDs)

FGDs will be conducted with VHTs and community leaders at baseline and endline. The goal of the FGDs with VHTs is to understand the type and structure of incentives that they prioritize. Community leaders will be engaged with the FGDs to provide an understanding of their relationship with VHTs as well as their perceptions of VHT activities in advancing health services. Between 9 and 10 FGDs will be held with VHTs and 9 and 10 with community leaders; there will be between 6 and 8 participants in each FGD. FGDs will continue until saturation is reached. Each FGD will have two trained facilitators: one will moderate the discussion and the other will take notes.

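### Objective 3 and the abstract promise an effect on community use of maternal and child services and on perceived quality, but no listed outcome measures ANC attendance, immunization status or perceived quality

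*Protocol article*

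**What the plan says.** All references are to the protocol article.

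- **Aims.** The third objective, at the end of Background, is "the impact of improved VHT performance on the utilization of maternal and child health services, hygiene practices, and perceptions regarding the quality"; the quality meant is how the community perceives its health services. The Abstract (Introduction) says the study evaluates the package's effect on VHT motivation, performance and retention, "as well as on the utilization of health services by the community". The opening of Methods/design is narrower: the trial is "to evaluate the effects of the intervention on the motivation, performance, and retention of VHTs in Uganda’s Masindi District", and use of services is not named.
- **Outcomes.** The primary outcome is VHT performance, "defined as the total number of home visits in the past three months". Table 1 adds four secondary groups: motivation, retention, a group titled "Other VHT performance (trends in service delivery", and sanitary practices per village.
- **Award criteria.** The section on the intervention ranks VHTs on three proportions. Two are coverage measures: children under five with up-to-date immunization, and "the proportion of women who attended at least four antenatal care visits". The third is the share of sick under-fives the VHT attended. Denominators are village population projections. None of the three proportions is listed as an outcome.
- **Discussion groups.** The Abstract (Methods) says "focus group discussions will be conducted with VHTs and community members". The section on focus group discussions (FGDs) says otherwise: "Community leaders will be engaged with the FGDs to provide an understanding of their relationship with VHTs". The Analysis plan intends to draw community perceptions, including those on quality of care, from these groups.

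**The concern.** An objective needs a measure that can answer it. Here the aim concerns what women and children in the community use and how services are perceived. The maternal and child items in the outcome list mostly record what the VHT did. A VHT can make more visits about antenatal care without any more women attending it, and can support immunization more often without more children being up to date.

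Two things are at stake. First, the maternal and child utilization part and the perceived-quality part of objective 3 would end the trial without a comparison between arms. Second, because the abstract has announced a utilization result, the nearest available counts could be read as one.

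The wording of objective 3 adds a smaller difficulty. It asks for the effect of improved VHT performance, whereas parishes are randomized to the incentive package. The planned regression and difference-in-differences analyses compare arms, so they estimate the effect of the package.

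**Working it through.** **The plan's only related figure.** The sample-size section gives a detectable difference of 12.5 home visits. Inputs: 16 parishes per arm, 15 responding VHTs per parish, SD 25, intra-class correlation 0.2, two-sided 0.05, power 0.8.

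- Design effect: 1 + (15 − 1) × 0.2 = 3.8.
- Effective number per arm: 240 / 3.8 = 63.2.
- Detectable difference: (1.960 + 0.842) × 25 × √(2 / 63.2) = 12.46.

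This agrees with the stated 12.5. It concerns home visits only and says nothing on use of services, so the point turns on matching aims to measures.

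**Count of Table 1.** Home visits 1, motivation scale 1, retention 1, outcome 4 items 8, outcome 5 items 5: 1 + 1 + 1 + 8 + 5 = 16 measures.

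The 8 items of outcome 4 divide evenly:

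- 4 count VHT actions: visits for antenatal care, visits for postnatal care, visits to support immunization, referrals made.
- 4 count recipients: sick under-fives attended, and people given HIV, TB or general counseling.

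**Objective 3 against the plan.**

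| Part of objective 3 | Measure in Table 1 | Elsewhere in the plan | Between-arm estimate? |
|---|---|---|---|
| Use of maternal services | Counts of VHT visits; no attendance measure | Proportion with four or more ANC visits, for awards only | No |
| Use of child services | Visits to support immunization; sick under-fives attended (a count) | Proportion up to date on immunization, for awards only | Not for immunization status; sick-child care by VHTs only |
| Hygiene practices | Outcome 5: five household counts | None needed | Yes |
| Perceived quality | None | FGDs with VHTs and leaders | No; qualitative only |

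**Data sources.** The quantitative sources are the VHT survey, the VHT phone survey and reports that VHTs submit to health facilities. No household or client survey is described. A utilization measure would have to come from VHT reports.

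**Can the two award proportions serve?** The intervention section says they were chosen because VHTs already record and report them. Facility reports are abstracted quarterly at four time points, and the text does not limit this to intervention parishes. Three features limit them as outcomes:

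1. The numerators are reported by unblinded VHTs, and only one arm is rewarded for high values.
2. Submitting the quarterly report is a condition for award consideration, and only intervention VHTs can win. Which villages have data may therefore differ by arm.
3. Denominators are per village, but awards go to individual VHTs. With 517 VHTs and 312 villages (517 / 312 = 1.7 per village), a VHT-level analysis could enter some villages more than once.

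**The case against.** The strongest reply is that the plan covers more of objective 3 than it first appears. Most of this stands, and it sets the limits of the point.

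- **Outcomes as VHT activity.** A reader might infer that every outcome counts the VHTs' own work. The document does not support that: outcome 5 counts households with latrines, handwashing facilities and safe water, which answers the hygiene part.
- **Outcome 4 and use of services.** A reader might infer that none of the eight items reflects anyone's use of a service. Four count recipients, and Background says VHTs themselves provide maternal, newborn and child services. A sick child attended by a VHT is a limited, VHT-reported measure of uptake without a denominator. Antenatal attendance and immunization status remain unmeasured as outcomes.
- **Perceived quality.** A reader might infer that it goes unanswered, or that no service user will be heard. The Analysis plan does include a qualitative reading of community perceptions, and nothing says that leaders are not also users. A head count of 9 × 6 = 54 to 10 × 8 = 80 community participants settles little: the text does not say whether 9 to 10 groups is per round, and groups continue to saturation.
- **Mislabelling.** No passage says outcome 4 will be reported as utilization; the article calls it performance and service delivery. This is a risk created by the abstract and is not a stated plan.
- **Wording of the effect.** The abstract already frames utilization as an effect of the package. Only objective 3 refers to improved performance.
- **Award proportions.** If they were adopted without caveat, reporting differences alone could produce an apparent effect. This stands and governs how they may be used.

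An analysis plan or fuller protocol may exist. The article nonetheless states both its objectives and its outcome list, and the two do not match, so this is more than detail left to another document.

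**Conclusion.** The mismatch holds for two parts of objective 3. Table 1 contains no population measure of ANC attendance or immunization status, and perceived quality has only a qualitative answer, from groups the article describes inconsistently. Neither part will have a between-arm estimate if the plan is followed as written. The hygiene part is covered.

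It would go too far to say that the trial cannot support any statement on utilization. Two coverage proportions are defined and could be compared between arms, with limits. The accurate statement is that the listed outcomes do not measure community use of maternal and child services.

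The primary outcome, its analysis and its power are untouched. The point should be corrected because it changes what the trial may conclude on an aim named in the abstract. It rests on reading Table 1 as the full outcome list, as the outcomes section presents it. That the proportions can be calculated in both arms further assumes that the quarterly form, which is not shown, carries their numerators, and that village projections are available for comparison parishes.

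**What to change.** 1. Reword objective 3 and the abstract as the effect of the randomized incentive package on VHT-reported service delivery and sanitary practices. Do not report outcome 4 counts as community utilization.
2. Add the two award proportions (up-to-date immunization; four or more ANC visits) as secondary, supportive outcomes. Compute each once per village, in both arms, from the quarterly reports already being abstracted. Record the date of the addition, since the article is dated 17 November 2022 and recruitment began in August 2021.
3. Label both as VHT-reported and award-linked, and show report-submission rates by arm beside them.
4. Reconcile community members in the Abstract with community leaders in the FGD section, and describe perceived quality as a qualitative finding from the groups actually held. Replacing leaders with service users is not required: it would weaken the baseline-to-endline comparison.

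The cost is wording, plus one further calculation on data already collected. The utilization claim becomes narrower, and the coverage measures remain open to differential reporting, so they cannot carry a firm conclusion alone.
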